**c) Dose adaptations****a) ATG-Fresenius S and Thymoglobulin dose adaptations**

Reduce to half the dose when leucopenia ( $2.000-3.000/\text{mm}^3$ ) and/or thrombocytopenia ( $50.000-75.000/\text{mm}^3$ ) are present

Withhold either drug when leukopenia ( $<2.000$ ) and/or thrombocytopenia ( $<50.000$ ) are present

**b) Tacrolimus target trough blood levels**

| Period                                                                                              | Whole blood 12 h trough level |
|-----------------------------------------------------------------------------------------------------|-------------------------------|
| Day 3 or 4 onwards, kidney well functioning                                                         | 10 - 12 ng/ml                 |
| Month 3 onwards, kidney well functioning, normal protocol biopsy                                    | 8 - 10 ng/ml                  |
| Month 6 onwards, kidney well functioning, normal protocol biopsy                                    | 6 - 8 ng/ml                   |
| Month 12 onwards, kidney well functioning, normal protocol biopsy                                   | 4 - 6 ng/ml                   |
| Rejection                                                                                           | Increase by 2 - 5 ng/ml       |
| Drug-toxicity (e.g. nephrotoxicity, infections, increased viral replication (i.e. EBV, Polyoma-BK)) | Decrease by 2 - 5 ng/ml       |

**c) Dose adjustment of MMF according to blood levels and leukocyte count**

| Period             | Dose adjustment of MMF according to blood levels and leukocyte count                                                           |
|--------------------|--------------------------------------------------------------------------------------------------------------------------------|
| From day 4 onwards | Blood levels should be preferably between 2 - 4 ng/ml                                                                          |
| From day 4 onwards | If leukocyte counts are below $3.500/\text{mm}^3$ : MMF has to be reduced according to the judgement of the treating physician |
| From day 4 onwards | If neutrophil granulocytes are below $800/\text{mm}^3$ : MMF has to be stopped                                                 |

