### 2.4.2 Pharmacokinetics

After an intravenous dose of 1.25 to 1.5 mg/kg/d (over 4 hours for 7-11 days) 4-8 hours post-infusion, Thymoglobulin levels were on average 21.5  $\mu\text{g/ml}$  (10 – 40  $\mu\text{g/ml}$ ) with a half-life of 2-3 days after the first dose, and 87  $\mu\text{g/ml}$  (23-170  $\mu\text{g/ml}$ ) after the last dose.

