**Two immunosuppressive protocols will be compared:**

1. a regimen consisting of a triple drug therapy with Tacrolimus, MMF, and steroids as basis therapy plus IVIG for 5 days (total dose 2g/kg bw, max. 140g). In addition, the patients receive intra-operative 9 mg/kg bw ATG-Fresenius S (completed before reperfusion), followed by 3 mg/kg bw/d for the next 4 consecutive days.

vs.

2. a regimen consisting of a triple drug therapy with Tacrolimus, MMF, and steroids as basis therapy plus IVIG for 5 days (total dose 2g/kg bw, max. 140g). In addition, the patients receive intra-operative 1.5 mg/kg bw Thymoglobulin (completed before reperfusion), followed by 1.5 mg/kg bw/d for the next 3 consecutive days.

After kidney transplantation in end stage renal disease patients it is assumed that:

- the safety profile of ATG-Fresenius S may be superior to that of Thymoglobulin
- the efficacy profile of both treatments is clinically equivalent

The aim is to obtain preliminary information on the safety and efficacy of two induction treatment protocols – ATG-Fresenius S and Thymoglobulin – in immunological high risk patients under basal immunosuppression with Tacrolimus, MMF and steroids used in the prevention of acute rejection following renal transplantation.

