### 6.2 Transplant monitoring

#### Standard monitoring:

- The patients will be followed by the routine clinical, biochemical and imaging parameters.
- Blood pressure, heart rate, temperature and urine output will be recorded daily during hospitalisation.
- Standard blood work as routinely done includes:
  - Complete blood count (including hemogram, leukocytes, reticulocytes and platelet count).
  - Complete blood chemistry (including serum creatinine, blood urea nitrogen (BUN), sodium, potassium, calcium, phosphate, uric acid, total protein, albumin, bilirubin, SGOT (AST), SGPT (ALT), LDH, gamma-GT, alkaline phosphatase, glucose, cholesterol and HbA1c).
- Standard blood work will be performed at each visit and at least at days 0, 1, 7, 14 and at months 1, 3, 6, 12 and 24.

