| Day 2                     | 3 mg/kg bw i.v. *                                                          | 0.4 g/kg bw                                                                                          | 0.2 mg/kg/d                                                | 2 x 1000 mg/d p.o                                           | 250 mg MP i.v.                                                                                  |
| Day 3                     | 3 mg/kg bw i.v. *                                                          | 0.4 g/kg bw                                                                                          | 0.2 mg/kg/d                                                | 2 x 1000 mg/d p.o                                           | 0.5 mg/kg/d p.o.
rounded to 5 mg (downwards)                                                 |
| Day 4                     | 3 mg/kg bw i.v. *                                                          | 0.4 g/kg bw                                                                                          | 0.2 mg/kg/d                                                | Dose adjustment to target blood levels and white cell count | Dose adaption (see below)                                                                       |
| Day 5                     | -                                                                          |                                                                                                      | 0.2 mg/kg/d then adjust to target blood levels (see below) | Dose adjustment to target blood levels and white cell count | Dose adaption (see below)                                                                       |
| Day 6                     | -                                                                          |                                                                                                      | Adjusted to target blood levels (see below)                | Dose adjustment to target blood levels and white cell count | Dose adaption (see below)                                                                       |

\* (dose adaptation see below)

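### The only MMF target level is printed in ng/ml, which does not fit 2 x 1000 mg/day if read as an average; the unit is probably wrong, and the line names neither the measured substance nor the sampling time

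*Protocol*

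**What the plan says.** Therapy schemes I and II (Protocol, section 6.4) give the same MMF: 2 x 1000 mg/day by mouth from day 0 to day 3. From day 4 the MMF column of both schemes reads "Dose adjustment to target blood levels and white cell count". The level meant is in table c) of the dose adaptations, headed "Dose adjustment of MMF according to blood levels and leukocyte count". Its first line, from day 4 onwards, is "Blood levels should be preferably between 2 - 4 ng/ml". The other two lines act on cell counts: reduce by judgement below 3,500 leukocytes/mm³, stop below 800 neutrophils/mm³.

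Table b), directly above, sets the tacrolimus targets. It also uses ng/ml, but it states matrix and sampling time: "Whole blood 12 h trough level". The MMF table states neither a sampling time nor which substance the assay measures. Section 6.2 lists the routine and optional monitoring and mentions no MMF level; it mentions no tacrolimus level either.

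**The concern.** A target blood level, a dose and a clearance are tied together by mass balance, so the printed target can be tested against the printed dose. Here a dose of grams per day is paired with a target of a few nanograms per millilitre. At 70 kg the daily MMF dose is about 143 times the tacrolimus dose (2000 mg against 14 mg), yet the MMF target is about a quarter of the tacrolimus target (midpoints 3 and 11 ng/ml).

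This is the one MMF level that sites in both arms are told to adjust to. The recipients have donor-specific antibodies (section 5.2). A site that took the line literally, and measured levels far above it, would be pointed towards a lower MMF dose. MMF exposure may bear on acute rejection (a secondary endpoint) and on leucopenia (a component of the primary endpoint).

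**Working it through.** **Inputs from the protocol**
- MMF dose: 2 x 1000 mg/day, so 2000 / 24 = 83.3 mg/h (therapy schemes I and II).
- MMF target: 2 to 4 ng/ml = 0.002 to 0.004 mg/L (dose adaptations, table c).
- Tacrolimus: 0.2 mg/kg/d, early target 10 to 12 ng/ml (therapy schemes; table b).
- Reference weight: the IVIG rule in section 3 ("total dose 2g/kg bw, max. 140g") caps the dose from 140 / 2 = 70 kg.

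**Assumptions, not in the documents**
- Fraction of the dose reaching the blood as the measured substance (F): 0.1 to 1.
- Total blood flow: 5 to 10 L/min = 300 to 600 L/h.
- For troughs: one compartment, rapid absorption, dosing every 12 h.

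**1. Target as printed, read as an average level.** CL/F = dose rate / average level.
- 83.3 / 0.004 = 20,833 L/h (347 L/min).
- 83.3 / 0.002 = 41,667 L/h (694 L/min).
- At F = 0.1, clearance is 2,083 to 4,167 L/h = 34.7 to 69.4 L/min. That is 34.7 / 10 = 3.5 times to 69.4 / 5 = 13.9 times the assumed blood flow.
- For clearance at or below blood flow with an average of 4 ng/ml, F could be at most 0.004 x 300 / 83.3 = 0.014 (5 L/min) or 0.004 x 600 / 83.3 = 0.029 (10 L/min).

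**2. Same figures in microgram/ml.** 83.3 / 4 to 83.3 / 2 = 20.8 to 41.7 L/h, well inside the assumed blood flow.

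**3. Cross-check on tacrolimus (supportive only).** It is a different drug, and its trough is used as if it were the average, so the result is an upper bound.
- At 70 kg: 14 mg/d = 583 microgram/h; 583 / 12 to 583 / 10 = 48.6 to 58.3 L/h.
- At 50 kg: 34.7 to 41.7 L/h. At 100 kg: 69.4 to 83.3 L/h.
- The MMF value in microgram/ml is of the same order. In ng/ml it is hundreds of times larger (20,833 / 58.3 = 357; 41,667 / 48.6 = 857).

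**4. Target read as a 12 h trough.** Trough = average x [x e^(-x) / (1 - e^(-x))], with x = 12 ln 2 / half-life. The trough is 4 ng/ml or less at half-lives up to:

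| F | Clearance | Average level | Half-life limit |
|---|---|---|---|
| 1 | 300 L/h | 278 ng/ml | 1.4 h |
| 0.1 | 300 L/h | 27.8 ng/ml | 2.7 h |
| 0.1 | 600 L/h | 13.9 ng/ml | 3.9 h |

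At a lower CL/F the half-life must be shorter: CL/F 40 L/h with a half-life of 1 h gives 4.2 ng/ml. With CL/F 10 to 90 L/h and a half-life of 2 h or more, the trough is at least 61 ng/ml.

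**5. Text extraction.** Micro signs survive elsewhere, for example in section 2.4.2, where "Thymoglobulin levels were on average 21.5" is followed by microgram/ml. Moreover, a dropped micro sign would leave g/ml, not ng/ml. A micro sign misread as the letter n cannot be excluded from the text alone; a look at the original page settles it.

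**The case against.** The strongest objection is that the decisive inputs come from outside the protocol. It gives no bioavailability, clearance, half-life or assay for MMF, and the conflict in step 1 disappears if less than about 1.4 to 2.9% of the dose is measurable. The neighbouring table also suggests a 12 h trough rather than an average, and step 4 shows that a trough of 4 ng/ml or less is then possible. Both points stand. They are why the wrong unit is probable and not proven. They do not rescue the line: either the unit is wrong, or the figure makes sense only for a substance and sampling time that the line omits.

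It can also be said that the practical risk is small. The target is only a preference, table c) prescribes no step that depends on the level, and section 6.2 schedules no MMF level. Treating physicians may well notice a large gap between measured level and target. This stands in part. However, both schemes do direct adjustment to target levels, and the silence of section 6.2 is weak reassurance, because it omits tacrolimus levels too although table b) clearly needs them.

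Three stronger readings are tempting. A reader might infer a proven error of a factor of 1000; the documents nowhere state the right unit, so this is an inference from plausibility and from the adjacent table. A reader might infer that patients will be heavily underdosed; no size of dose cut can be derived. A reader might infer a biased comparison; the MMF instruction is the same in both arms, so none follows from the text.

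**Conclusion.** The point holds in a limited form. Read as an average level at the protocol's own dose, the MMF target requires a clearance 3.5 to 14 times an assumed blood flow of 5 to 10 L/min, even with F as low as 0.1. Read in microgram/ml, it requires 21 to 42 L/h. The printed unit is therefore probably wrong, and a carry-over from the tacrolimus table is the likeliest source. The conclusion rests on the assumed F and blood flow and on the average-level reading; a low 12 h trough with a short half-life remains possible. What is certain is that the line leaves out the measured substance and the sampling time, so it cannot be applied safely as it stands. This is a matter of dosing safety in a high-risk population. It does not touch the sample size, the analysis or the comparison between arms.

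**What to change.** The sponsor checks the unit against the MMF assay used at the centres. The first line of table c) then restates the target in the confirmed unit (expected: microgram/ml, that is mg/l), with the measured substance and the sampling time, in the way table b) does for tacrolimus. The corrected line goes to both centres. The unit should not be changed before the assay check, because the documents do not settle it. The cost is one amended table line, with no added procedure.

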**d) Tapering steroid dosage**

Starting at day 3 with 0.5 mg/kg bw, tapered by 5 mg biweekly until 15 mg, then by 2.5 mg biweekly until 0.1 mg/kg until month 6. In case of rejection, steroids may be increased at the discretion of the responsible physician. Steroids can be withdrawn after month 6 at the discretion of the responsible physician.

**6.5 Procedures for monitoring subject compliance**

ATG-Fresenius S and Thymoglobulin must only be administered according to the instructions of a physician and under medical supervision. This avoids a deviation from compliance by the patient. The physician in charge is responsible to document the applied amount of ATG-Fresenius S/ Thymoglobulin in the CRFs.

## 6.6 Handling of the investigational drug

- a) Rules for the use of concomitant treatment:  
Sodium Heparin must not be added to the ATG-Fresenius S infusion solution or administered via the same route, because a pH below 5.2 may lead to turbidity.
- b) Measures to be implemented to ensure the safe handling of the drugs, measures to control close adherence to the instructions:  
ATG-Fresenius S is a hypotonic concentrate for infusion with pH 3.7. Before intravenous infusion it must be diluted with physiological saline solution.  
ATG-Fresenius S must only be administered according to the instructions of a physician and under medical supervision. Particular attention must be paid to monitoring the patient for any symptoms of anaphylactic shock. Close monitoring of the patient must continue for at least 30 minutes following the end of the infusion.  
For peripheral administration a large vessel should be chosen. It has been found that systemic tolerance is improved, if hydrocorticosteroids and/or antihistaminic drugs are administered prior to infusion.

- c) Thymoglobulin  
The powder should be mixed with the solvent that is added in the package. Thymoglobulin is infused after dilution in saline (0.9%) or dextrose (5%) solution (per one vial use 50 ml of infusion solution). Mix the solution by inverting the bag gently once or twice.  
Infuse slowly into a high-flow vein. Adjust the infusion rate so that the total duration of infusion is at least one hour for the first dose and over at least 4 hours for subsequent doses.

### Instructions for Administration:

The recommended route of administration is intravenous infusion using a high-flow vein and should be infused over at least one hour for the first infusion and over at least 4 hours on subsequent days. The calculated number of Thymoglobulin vials should be transferred into a bag of infusion solution (0.9% saline or 5% dextrose) before intravenous administration to patients. When mixing the solution, gently invert the bag only one or twice: DO NOT SHAKE.

Inspect solution for particulate matter after reconstitution. Should some particulate matter remain, continue to gently rotate the vial until no particulate matter is visible. If particulate matter persists, discard this vial.

Do not use Thymoglobulin after expiration date indicated on the label.

Any unused portion of the drug must be discarded.

Once the infusion is prepared, it should be used within 4 hours after reconstituting if kept at room temperature.

## **7. ASSESSMENT OF SAFETY**

### **7.1 Specification of safety parameters**

All adverse events reported will be included in the safety evaluations with particular attention to the list mentioned in chapter 4.3.1. All symptoms will be inquired actively.

### **7.2 Methods and timing for assessing, recording, and analysing of safety parameters**

Adverse events, reported by the patient and/or observed by study personnel, will be summarized for each treatment group. Laboratory data will be compared to the corresponding normal ranges. Physiopathologically relevant high or low parameters will be summarized for each treatment group. Per protocol all AE documentation is performed continuously.

### **7.3 Procedures for eliciting reports of and for recording and reporting adverse events and intercurrent illnesses**

Definitions:

- a)** Adverse drug reaction: A response to a drug which is noxious and unintended and which occurs at doses normally used in man for prophylaxis, diagnosis or therapy of disease or for modification of physiological function.  
It should be considered, that „death“ per se is no adverse drug reaction, but may be the consequence or the outcome of an event, which may be an adverse drug reaction and which should be assessed. If the reason of death is unknown and remains unknown despite proper investigation, the phrase „inexplicable death“ may be used to describe the reaction.
- b)** Serious adverse drug reaction  
A serious adverse drug reaction is a drug reaction, which results in death, is life-threatening, requires inpatient hospitalisation or prolongation of existing hospitalisation, or results in persistent or significant disability/incapacity.
- c)** Unexpected adverse drug reaction  
An unexpected adverse drug reaction is an adverse drug reaction, which is not mentioned in the Summary of Product Characteristics, the package insert, the Scientific Brochure, the Investigator's Brochure, the protocol or elsewhere.
- d)** Unexpected serious adverse drug reaction  
An unexpected serious adverse drug reaction is defined as an adverse drug reaction, which is unexpected as well as serious.
- e)** Adverse event  
An adverse event is any untoward medical occurrence in a patient, who was treated with a pharmaceutical product, independent if there is a causal relationship with the administration of the drug suspected or not.

**f) Serious adverse event**

Serious adverse events are adverse events, which result in death, are life-threatening, require inpatient hospitalisation or prolongation of existing hospitalisation, result in persistent or significant disability/incapacity. A congenital anomaly/birth defect or malignancy are usually be considered serious.

**g) Causality assessment**

The causal relationship to the study medication has to be assessed for every adverse event using one of the following terms:

**1 = probable**

- reasonable temporal sequence after administration of study medication
- the AE has already been described or can be expected as a side effect of the drug
- decrease or disappearance of symptoms after discontinuation of treatment or dose reduction
- renewed appearance of the AE after repeated exposure to the study medication
- no reasonable explanation of the AE via the patient's clinical condition

**2 = possible**

- reasonable temporal sequence after administration of study medication
- the AE has already been described or can be expected as a side effect of the drug
- the AE may be caused by several other reasons

**3 = unlikely**

- reasonable temporal sequence after administration of study medication
- the AE has not yet been reported as a side effect of the drug and cannot be expected
- the AE remains persistent after discontinuation of treatment or dose reduction
- repeated exposure to the study medication does not lead to the same event
- the AE may be caused by several other reasons

**4 = no relationship**

- no reasonable temporal sequence after administration of study medication
- the AE has obviously been caused by other reasons, e.g. symptoms of the study indicating disease itself

**5 = assessment impossible**

- the available data are insufficient for any reasonable assessment with respect to a causal connection

In this open-label trial the causality assessments of all adverse events will be provided by blind raters. The rater will receive all information available for a particular adverse event, including predisposing factors from the patients' history, concomitant medication and diseases, but he/she will be unaware of the investigational treatment actually received. For each adverse event two different causality assessments will be obtained: (a) assuming that the patient has received ATG and (b) assuming that he/she has received Thymoglobulin. During data analysis only the assessment corresponding to the treatment actually received will be used.

All cases where 1, 2 or 3 applies will be evaluated as attributable adverse events / ADRs.

All adverse events, i. e. also the already known ADRs, must be documented and serious adverse events also be registered. There is also an obligation to registration if a causal relationship is not supposed resp. not evident. The following items must be registered:

- Precise trial subject data;
- precise description of the AE;
- precise recording of the time of the AE in relation to the course of therapy;
- intensity of the AE;
- results of diagnostic and therapeutic measures,
- where applicable, rechallenge and/or dechallenge data;
- course and outcome of the AE;
- severity of the AE, including medical assessment;
- all other important data that may be of relevance for assessment of a possible relationship between the AE and the administration of the investigational medical substance.

Data are documented and registered on the form "adverse events" or „serious adverse events“ (see enclosure 4), whereby the needed additional information can be supplied without a specific form.

#### **h) Intensity assessment**

The intensity of an AE is to be graded using the terms mild, moderate, and severe. These are defined as follows:

- Mild:           the event is realized but well tolerated  
Moderate:   the event interferes with usual daily activities  
Severe:       the event makes usual daily activities impossible

**Note:** A strict difference is to be made between intensity grading and whether an adverse event is serious or not. A highly pronounced AE needs not necessarily be serious.

